#### Patient feedback

At the end of the navigation, for quality improvement purposes, patients will be asked to complete a Patient Satisfaction Survey with Likert scale responses for overall satisfaction, specific program components, and likelihood of recommending the program to friends and family.

### Measures and outcomes

#### Primary outcome

Our primary effectiveness outcome is clinic-level CRC screening completion rates every six-months for Black and Hispanic/Latino patients aged 45 to 75 years old comparing intervention and control conditions (within and across clinics). Our grant partner, the National Committee on Quality Assurance (NCQA) will lead translation of the HEDIS® colorectal cancer screening (COL) quality measure from the Fast Healthcare Interoperability Resources data model into the Observational Medical Outcomes Partnership (OMOP) common data model, supporting efficient, reliable, outcome measurement to support translation of findings into policy-aligned practice. This will include development of all existing COL cohort definition in ATLAS, [41] creation of the ATLAS concepts (using the HEDIS Value Set Directory as a primary reference, without external publication or replication of those value sets), and creation of the COL artifacts for implementation in the MedStar Health dataset. Definitions and concepts will undergo iterative review with both NCQA and MedStar Health teams to ensure accuracy and implementation feasibility. These Observational Health Data Sciences and Informatics query definitions can be run at any institution and will be made publicly accessible. All data on completion of CRC screening by race and ethnicity will be extracted from the EHR under a HIPAA waiver. We will also consider intersectional characteristics of participants such as age and payor in addition to race and ethnicity. We will compare EHR data extracted manually to follow quality metric standards with data obtained through the OMOP Common Data Model to cross-validate results.

#### Secondary outcomes

We will also assess implementation outcomes including reach and adoption of the culturally tailored navigation intervention. Reach will be assessed as the percentage of eligible Black and Hispanic patients at each clinic who received a referral for navigation, and of those referred, who engaged with navigation. While we will look at overall reach, we will also calculate the number of people referred among those who have previously failed to complete screening referrals/orders to better understand navigation referral for those who are at higher risk of non-compliance. We will consider intersectional factors affecting reach such as patient insurance, age, race/ethnicity, and primary language. Adoption will be assessed by the percentage of providers who referred eligible patients for navigation. Each of these outcomes will also be examined separately for Black and Hispanic/Latino patients.

We will solicit feedback from clinical champions both on patient navigation and the implementation strategies (engaging patients, clinic assessments and tailoring, audit and feedback loops) via annual surveys. Surveys will include questions on acceptability, feasibility, and appropriateness using a validated 12-item scale, [42] the Clinical Sustainability Assessment Tool, [43] questions on satisfaction with the SCREEN programs, and suggestions for improvement. At the end of the trial, we also will conduct interviews with one or two representatives from each clinic site to understand how the intervention and implementation strategies addressed or failed to address contextual barriers to navigation implementation.

To track changes to the implementation strategies, or clinic-level delivery of navigation, we will adopt the Longitudinal Implementation Strategy Tracking System (LISTS, Table 4) [44], which incorporates implementation science strategy reporting and specification standards, [45] and the framework for documenting modifications to implementation strategies (FRAME-IS), [46] to understand how an intervention is being delivered and iteratively adapted across diverse settings. These methods will support the documentation of the implementation strategies so that we can better understand implementation of a patient navigation program for historically underserved populations across clinics with different baseline characteristics.

##### Navigation fidelity

Navigators will track phone calls in REDCap [47]. The REDCap form will include a structured list of key components that should be covered by type of phone call (Supplemental Table 1), and the navigator will select each of the key components that were covered in the phone call. We will also conduct fidelity checks of navigation bi-annually by a research team member observing a randomly selected 5% of phone calls with a structured checklist to record fidelity to the prescribed intervention.

##### Patient-level

We will conduct online surveys in years 2 and 4 across all 15 clinics to understand patient experiences of care using the Discrimination in Medical Setting Scale [48] via REDCap. At Year 2, we will survey 20 patients per clinic (*n* = 300) who have not undergone navigation and in Year 4 we will survey 20 patients per clinic (*n* = 300) who completed navigation. In Year 4, we will also include a survey about acceptability of the navigation and open-ended questions about the navigation experience and appropriateness of cultural tailoring. During the intervention phase in Years 2 to 4, we will interview 10–15 patients a year who complete navigation, to understand experiences in navigation and to get feedback on the intervention.

### Data analysis plan

Baseline characteristics of the patients in the intervention and control groups will be summarized first in a traditional way (intervention vs control) using means, standard deviations for continuous variables and frequencies and percentages for categorical variables. Exploratory descriptive analyses will also be conducted using clinic level data for six-month periods to examine patient characteristics to ensure a balanced design in an intent-to-treat (ITT) framework. Initial comparisons between the intervention and control groups will be done using two-sample test statistics such as t-test and Chi-square as appropriate. The effectiveness of the intervention will be assessed based on the primary patient-level outcome, screening completion, which is measured as a binary variable indicating whether a patient identified as “due for screening” completed CRC screening, and will be analyzed using Generalized Linear Latent and Mixed Models [49] suitable for categorical, ordered or count outcomes with random effects at multiple levels since observations will be nested in clinics and clinics will be exposed to intervention at different time points. The model will include a treatment indicator, a fixed effect for time (steps) and their interactions to account for the potentially confounding effect of varying crossover timepoints for clinics. The model will also include patient characteristics (Black or Hispanic/Latino, age, sex, payor) as well as random effects for clinics. Secondary patient and clinic level outcomes will be described and compared between intervention and control groups using the methods described earlier. We will also include Area Deprivation Index in the models as appropriate, calculated based on 2020 census data. Analyses will be conducted in Stata or R. All analyses will consider sex as a biological variable and race as a social construct.

The study was powered to detect a significant difference in the CRC screening rates between Black and Hispanic/Latino patients who receive navigation services and those who do not receive navigation. The design consists of 15 clusters and 6 steps (one baseline all clusters in control condition + 5 intervention steps) of six-month duration where 3 clusters will switch to intervention every 6-month. A sample size of an average of 120 participants (60 intervention and 60 control) per cluster and an average of 20 participants per cluster/step will achieve 80% power with 1800 participants (900 navigation and 900 control participants) to detect a conservative 10-percentage point difference in the primary outcome measure of CRC screening completion. The navigation intervention is expected to increase the screening rate from an average 60% (current data across clinics) to an average of 70%. The test statistic used was the two-sided Wald Z-test, the intra-class correlation (ICC within-clinic) was assumed to be 0.05 and the Type I error was 0.05. Sample size calculations were conducted in PASS 15 [50]. Since the navigation will be applied to all referrals and we will obtain screening completion data from EHR, this sample size will be considered as the minimum number of patients to achieve the anticipated effect size.

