#### Cluster-randomized controlled trial

The statistician (MM) will randomize all clinics stratified by clinic size (categorized as small, medium, large number of Black and Hispanic/Latino patients due for screening) into five, six-month steps (three clinics per step) (Fig. 2). In the stepped wedge design, after a six month baseline period where all clinics are in the control arm, clinics will cross-over to the intervention condition in sequential, staggered fashion with three clinics per step until all clinics have received the intervention. In each step, clinics randomized to intervention will receive focused implementation support for six months to tailor the patient navigation program. After the six-month step, clinic patients will continue to receive navigation and providers will continue to receive reminders and communication, but feedback will move to a quarterly cadence.

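### The primary model includes treatment-by-step interactions but names no contrast that yields the single overall effect the trial was powered for

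*Protocol article*

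**What the plan says.** The Data analysis plan analyses a patient-level binary outcome, screening completed or not, in a generalized linear latent and mixed model. For the fixed part it states: "The model will include a treatment indicator, a fixed effect for time (steps) and their interactions to account for the potentially confounding effect" of clinics crossing over at different times. Patient characteristics are added, "as well as random effects for clinics". No contrast, reference step or averaging rule is given.

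The design is fixed elsewhere in the article. Under Cluster-randomized controlled trial, clinics cross over "after a six month baseline period where all clinics are in the control arm", with "three clinics per step until all clinics have received the intervention". The sample size paragraph agrees: "The design consists of 15 clusters and 6 steps (one baseline all clusters in control condition + 5 intervention steps"), where "3 clusters will switch to intervention every 6-month".

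That paragraph powers one overall difference, 60% against 70%, with a two-sided Wald Z-test, an ICC of 0.05 and a Type I error of 0.05: "an average of 20 participants per cluster/step will achieve 80% power with 1800 participants (900 navigation and 900 control participants"). It mentions no interaction and no step-specific effect.

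On what changes after crossover, the article says that after a clinic's first six months "clinic patients will continue to receive navigation and providers will continue to receive reminders and communication, but feedback will move to a quarterly cadence".

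**The concern.** A treatment-by-step interaction gives every calendar step its own treatment effect. Two of the six steps cannot supply one: baseline has no treated clinic and the last step has no control clinic. Once the interactions are in the model, the coefficient labelled treatment is no longer an overall effect, and its meaning depends on how step is coded.

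The rationale does not support the interactions either. Confounding by calendar time arises because treated clinic-periods fall later than control ones, and the step main effects deal with that. The interactions only let the effect differ between steps.

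At stake is what the primary result is. Two analysts following the sentence could report different coefficients as the trial's effect, neither being the quantity the sample size was set for.

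**Working it through.** **Inputs (all from the article).** 15 clinics; 6 steps counting baseline as step 1; three clinics crossing at each later step; 20 patients per clinic and step; 60% against 70%; ICC 0.05; two-sided alpha 0.05. Clinics on intervention at steps 1 to 6: 0, 3, 6, 9, 12, 15.

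**1. Reproducing the stated 80%.** Take a constant effect, additive step effects and a random clinic intercept, on a linear-probability approximation (Hussey-Hughes variance):

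Var = I·s²·(s² + T·τ²) / [(I·U − W)·s² + (U² + I·T·U − T·W − I·V)·τ²]

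- I = 15, T = 6.
- U = 45 treated clinic-steps.
- W = 0 + 9 + 36 + 81 + 144 + 225 = 495.
- V = 3 × (25 + 16 + 9 + 4 + 1) = 165.
- I·U − W = 675 − 495 = 180.
- U² + I·T·U − T·W − I·V = 2025 + 4050 − 2970 − 2475 = 630.

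With total variance 0.70 × 0.30 = 0.21:
- s² = 0.95 × 0.21 / 20 = 0.009975; τ² = 0.05 × 0.21 = 0.0105.
- Var = 0.010919 / (1.7955 + 6.615) = 0.001298, so SE = 0.0360.
- Power = Φ(0.10/0.0360 − 1.96) = 79.3%.

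With the pooled variance 0.65 × 0.35 = 0.2275, the SE is 0.0375 and power 76.0%. The stated 80% is thus matched, to within a point on the first convention, by a model **without** interactions.

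**2. Rank of the model as written, step categorical.** Columns: intercept 1 + steps 5 + treatment 1 + interactions 5 = 12. There are two exact dependencies:
- treatment × step 6 equals the step 6 indicator, because every clinic is then treated;
- the interactions for steps 2 to 6 sum to the treatment indicator, because nobody is treated at step 1.

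The rank over the 90 clinic-steps is 10. Effects at steps 2, 3, 4 and 5 are estimable; those at steps 1 and 6 are not. With baseline as reference, the treatment coefficient is the step 1 effect and is not estimable. If the software drops terms, it becomes the effect at whichever step is left. The dependency lies in the design matrix, so a logit link or patient covariates do not remove it.

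**3. Precision of what remains.** Generalized least squares with the same variance components; power = Φ(0.10/SE − 1.96):

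| Quantity | SE (total variance 0.2275) | Power | SE (0.21) | Power |
|---|---|---|---|---|
| Constant effect, no interaction | 0.0375 | 76.0% | 0.0360 | 79.3% |
| Effect at step 2 or step 5 alone | 0.0733 | 27.6% | 0.0704 | 29.5% |
| Effect at step 3 or step 4 alone | 0.0602 | 38.3% | 0.0578 | 40.9% |
| Linear step and linear interaction, effect at baseline | 0.0585 | 40.1% | 0.0562 | 42.8% |
| Categorical step, linear interaction, effect at baseline | 0.0866 | 21.0% | 0.0832 | 22.4% |
| Equal-weight average of steps 2 to 5 | 0.0380 | 74.8% | 0.0365 | 78.1% |

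Weights 0.2/0.3/0.3/0.2 on steps 2 to 5 return the constant-effect SE exactly. A linear interaction with step centred mid-trial (3.5) also keeps the constant-effect power.

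**4. Time since crossover.** If the effect changes with exposure, the constant-effect coefficient weights the effects in the first to fifth step after crossover by 0.78, 0.36, 0.07, −0.09 and −0.11. Negative weights mean it is not a proper average. Splitting treatment into the first step after crossover and later steps gives SEs of 0.038 and 0.048 (variance 0.2275).

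**The case against.** A reader might infer that a stepped wedge cannot identify treatment-by-step effects, so the model yields no overall estimate. The design does not support that. Steps 2 to 5 have 3, 6, 9 and 12 treated clinics beside concurrent controls, so four step-specific effects are identified, and their average costs about one point of power. What is missing is the sentence naming that average.

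A reader might also infer that the trial loses more than half its power. That requires taking one raw coefficient as the primary test, which the article does not say. It also fails for some codings: 40.9% at steps 3 and 4 and 42.8% for the linear coding are more than half of 79.3%. Moreover, 20 per clinic and step is described as a minimum. Assuming 60 instead, single-step power is 65-81% (variance 0.2275).

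The purpose clause can be read as governing the whole list of terms, in which case the step effects do answer the confounding. That reading is fair, but it leaves the interactions without a stated purpose.

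Finally, a separate analysis plan may name the contrast. It may, and it is not available here. But the article goes beyond leaving detail open: it states a primary model whose treatment coefficient does not match its own power statement.

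**Conclusion.** The point holds in limited form. The stated primary model has no single treatment coefficient equal to the 10-point difference that was powered, because baseline and final-step effects are aliased with step (rank 10 of 12) and no contrast over steps 2 to 5 is named. Read off directly, the treatment coefficient has about 28-41% power for a single step and 21-43% for the uncentred linear codings, against 76-79% for a constant effect.

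The rank result depends only on the design. The power figures assume a linear-probability scale, equal cells of 20, ICC 0.05, no clinic-by-period correlation and total variance 0.21 to 0.2275; larger cells would raise them.

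**What to change.** Define the primary analysis as one treatment coefficient with categorical step fixed effects, the random clinic effect and the listed covariates, without treatment-by-step terms. This matches the sample size statement. Move the interaction to a secondary analysis of heterogeneity. Alternatively, keep the interaction and name the average over steps 2 to 5, with its weights, as the primary contrast, at 75-78% power with equal weights.

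In either case, pre-specify a sensitivity analysis by time since crossover, separating the first six months from later steps. The article says that support changes at that point, and a calendar-step interaction does not represent it. Reword the rationale so that calendar-time confounding is assigned to the step main effects.

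The cost is wording, with no change to design or data. The small downside of the first option is that calendar-step heterogeneity leaves the primary test. The choice should be recorded before outcome data are analysed.

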### Patient navigation- Patient-level component

#### Patient eligibility and initial CRC outreach

Patients will be eligible if they are 45 to 75 years old, identify as Hispanic/Latino and/or Black, are not up to date on CRC screening recommendations, and have had at least one primary care visit at the included clinics in the past 365 days. The target population of patients who are due for screening is intended to align with the quality metrics relevant to CRC screening in the healthcare system. While we are not limiting to annual well visits, we will conduct sensitivity analyses to understand how reason for a visit affects screening referral, navigation referral, or completion outcomes. For clinics in the intervention phase, the provider will have the option to refer patients to navigation. Two days prior to their primary care appointment, patients will receive a reminder via text message indicating that their CRC screening is due and encouraging them to talk to their doctor about CRC screening.

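### The primary model names random effects for clinics only; if no clinic-by-step term is fitted and clinic rates drift differently over three years, the treatment standard error is too small

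*Protocol article*

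**What the plan says.** The Data analysis plan specifies a generalized linear latent and mixed model for a patient-level binary outcome. Its fixed effects are treatment, step and their interaction. It then says: "The model will also include patient characteristics (Black or Hispanic/Latino, age, sex, payor) as well as random effects for clinics". An earlier sentence describes the model class as allowing random effects at more than one level. The reasons it gives are that patients sit within clinics and that clinics cross over at different times. Clinics are the only level named as having a random effect.

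The sample size paragraph of the same section describes the design: "The design consists of 15 clusters and 6 steps (one baseline all clusters in control condition + 5 intervention steps) of six-month duration". Its planning size is "A sample size of an average of 120 participants (60 intervention and 60 control) per cluster and an average of 20 participants per cluster/step", which "will achieve 80% power with 1800 participants (900 navigation and 900 control participants) to detect a conservative 10-percentage point difference". The rate is expected to "increase the screening rate from an average 60% (current data across clinics) to an average of 70" per cent. On correlation it says: "The test statistic used was the two-sided Wald Z-test, the intra-class correlation (ICC within-clinic) was assumed to be 0.05". No correlation between steps is given. Because outcomes come from the health record, the paragraph treats this sample size as a minimum.

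Under Cluster-randomized controlled trial, clinics are randomised "stratified by clinic size (categorized as small, medium, large number of Black and Hispanic/Latino patients due for screening". The listed model terms do not include that stratum.

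**The concern.** A clinic random intercept with no further term assumes that two patients of one clinic are equally correlated whether they are seen in the same step or three years apart. Fixed step effects remove only shifts shared by all clinics. A change confined to one clinic between steps is then counted as binomial noise. Binomial noise shrinks as patients per clinic-step increase, but a clinic-specific shift does not. The fitted standard error therefore falls further below the true one as the data grow.

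The validity of the primary comparison is at stake. In a stepped wedge much of the information on the treatment effect comes from within-clinic changes between steps, which is where the unmodelled variation sits.

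**Working it through.** **Inputs from the article:** 15 clinics, 6 steps, 3 clinics crossing at each of steps 2 to 6, m = 20 per clinic-step, 60% against 70%, ICC 0.05, two-sided alpha 0.05. **Assumptions:** CAC of 0.95, 0.9 or 0.8, and m of 100 or 200 as illustrations of larger record-based numbers. The article gives neither.

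**1. The article's own power.** Clinic intercept and fixed steps, generalised least squares, CAC = 1. The outcome variance is averaged over the arms: (0.6×0.4 + 0.7×0.3)/2 = (0.24 + 0.21)/2 = 0.225. The standard error is 0.0373, so power = Φ(0.10/0.0373 − 1.96) = 76%. With the variance at 70% (0.21) the standard error is 0.0360 and power is 79%. The stated 80% is therefore close to reproduced, on the most favourable variance choice. It contains no clinic-by-step component.

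**2. A truth with drift.** Write s² = 0.225 and split the variance of a clinic-step mean into three parts:
- clinic: ICC × CAC × s²
- clinic-by-step: ICC × (1 − CAC) × s²
- patients: (1 − ICC) × s² / m = 0.21375/m

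At CAC 0.8 the clinic-by-step part is 0.05 × 0.2 × 0.225 = 0.00225, whatever m is. The patient part is 0.0107 at m = 20 and 0.00107 at m = 200.

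**3. What the clinic-intercept model reports.** Its residual variance converges to 0.21375 + 5m × 0.00225/(6m − 1), about 0.2156. At m = 200 it therefore gives a clinic-step mean a within-clinic variance of 0.2156/200 = 0.00108. The true value is 0.00107 + 0.00225 = 0.00332. The square root of 0.00108/0.00332 is 0.57, which is roughly the factor by which the standard error is understated.

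**4. Full calculation.** The model-based standard error is compared with the sandwich (true) standard error of the same estimator. Type I error = 2Φ(−1.96 × model SE / true SE).

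| CAC | m = 20 | m = 100 | m = 200 |
|---|---|---|---|
| 1.0 | 5.0% | 5.0% | 5.0% |
| 0.95 | 5.5% | 8.0% | 11.2% |
| 0.9 | 6.1% | 11.0% | 16.9% |
| 0.8 | 7.1% | 16.7% | 26.2% |

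At CAC 0.8 the model and true standard errors are 0.0372 and 0.0404 (m = 20), 0.0173 and 0.0245 (m = 100), and 0.0123 and 0.0215 (m = 200).

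**5. Checks.** Logistic random-intercept simulations, 1,500 runs per cell, gave the following for CAC 0.95, 0.9 and 0.8: 5.1%, 5.5% and 6.7% at m = 20; 8.3%, 10.7% and 17.2% at m = 100; 11.5%, 16.7% and 26.9% at m = 200. Adding the planned treatment-by-step interactions and averaging the effect gives the same inflation as the table. The result is sensitive to the ICC: at CAC 0.9 and m = 200 it is 7.2% at ICC 0.01, 9.7% at 0.02, 16.9% at 0.05 and 27.2% at 0.10.

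**6. With a clinic-by-step effect fitted** (REML on clinic-step means, m = 20 and 200, CAC 0.95 and 0.8, 1,500 runs each), type I error is 5.3-5.8% with a normal reference, 4.9-5.5% with t on 69 degrees of freedom and 3.1-3.8% with t on 13. Power at m = 20 under the correct model is 76% at CAC 1, 73% at CAC 0.9 and 70% at CAC 0.8.

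**The case against.** The article never says that a clinic intercept is the only random effect. Its reference to several levels could cover a clinic-by-step term, and an analysis plan not shown may contain one. This stands as a reason to word the point conditionally. It does not remove it: the article lists the terms of its primary model, clinics are the only level named, and the power calculation uses one ICC.

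Inflation also needs a CAC below 1, which the article does not give, and at the documented 20 per clinic-step it is small. Both objections stand.

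A reader might infer four stronger things that the documents do not support:
- **That the analysis will use a Wald Z-test.** That statement describes the sample size calculation. No reference distribution is fixed for the analysis.
- **That the article itself expects clinic-specific drift.** The Background lists turnover among clinic characteristics that may shape a programme. Clinic eligibility and recruitment mentions it as the reason one clinic declined. The Discussion describes system-wide and national trends, which fixed step effects largely absorb. Drift is plausible over three years but is not stated.
- **That a patient-level random effect is required.** Eligible patients must "have had at least one primary care visit at the included clinics in the past 365 days", a window longer than one step, so a patient could qualify twice. The article does not say how patients are assigned to steps. Someone who stays due until screened and then leaves resembles discrete-time event data, where repeated rows do not by themselves call for such a term. No size was worked out for this.
- **That omitting the size stratum makes standard errors too small.** Including it, if it explains 20-50% of between-clinic variance, cuts the standard error by only 1-3%. Omitting it costs a little precision.

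**Conclusion.** The point holds in conditional form. The model as named, and the single ICC behind the power figure, make no allowance for within-clinic correlation to weaken across six steps. If it is fitted that way and CAC is below 1, the error rate of the primary test exceeds its nominal level, by an amount that grows with patients per clinic-step.

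At the planned size the excess is modest. It becomes serious at 100 or 200 per clinic-step, sizes that the article neither states nor rules out. The figures rest on ICC 0.05, equal clinic-step sizes, a clinic-plus-clinic-by-step truth and the assumed CAC range. It would be wrong to say that type I error will certainly exceed 5%, or that numbers will certainly be far above 20.

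The change is worth making before analysis, because a CAC of exactly 1 is the special case that would need defending.

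**What to change.** State in the primary model a clinic-by-step random intercept in addition to the clinic random effect. Name in advance a reference distribution or small-sample correction suited to 15 clusters, or a permutation test over the randomised sequences. The choice matters: in the check above, t on 13 degrees of freedom was conservative and t on 69 was close to nominal. Add the clinic-size stratum used in the randomisation as a fixed effect, for a small gain in precision only.

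Restate power with the clinic-by-step component over a stated CAC range, say which outcome variance was used, and give the number of due patients expected per clinic-step.

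The cost is a few lines of specification, slightly wider intervals and a stated power below 80% at 20 per clinic-step. Larger numbers would more than recover that power: under the correct model at CAC 0.8 it is about 98% at 100 per clinic-step.
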